#### Treatment group intervention (PSD with a real needle)

For the active treatment group, bilateral PC5, PC6, ST36, ST37, KI3, and SP6 will be stimulated 20 min per day for 5 days using disposable, sterile needles inserted to a depth of 1.5 ± 0.5 cm, and connected to an electrical stimulator (ES-160, ITO, Japan) with a frequency of 2 Hz. Acupuncture points were selected according to experimental/clinical articles, classic acupuncture and meridian theory, clinical experience, and consensus of the Korean Medicine Doctor (KMD) [15–23]. PC5, PC6, ST36, and ST37 are already known to be effective in cardiac disease [15, 16]. As our primary outcome is the total diuretic dose, acupuncture points that have the effect of decreasing diuresis and edema (KI3, SP6) were also selected. Other detailed information of the acupuncture treatment regimen is described in the STandards for Reporting Interventions in Clinical Trials of Acupuncture (STRICTA) checklist [35] (Table 2).

**Table 2 Tab2:** Details of acupuncture treatments based on the STRICTA 2010 checklist

Item		Detail
1. Acupuncture rationale	1a) Style of acupuncture	Electroacupuncture based on traditional Korean medicine theory
	1b) Reasoning for treatment provided, based on historical context, literature sources, and/or consensus methods, with references where appropriate	Based on consensus of the KMD, clinical experience, traditional acupuncture, meridian theory, and experimental/clinical articles
	1c) Extent to which treatment was varied	All participants will receive standardized treatment
2. Details of needling	2a) Number of needle insertions per subject per session	12
	2b) Names of points used	bilateral PC5, PC6, ST36, ST37, KI3, and SP6
	2c) Depth of insertion, based on a specified unit of measurement	1.5 ± 0.5 cm
	2d) Response sought	De-qi
	2e) Needle stimulation :	Electrical stimulation with a frequency of 2 Hz, 400 μs per stimulation (ES-160, ITO, Japan)
	2f) Needle retention time	20 min
	2 g) Needle type	Park Sham Device (PSD) with a real needle; 0.20 mm × 40 mm sterilized stainless steel needle (Park Sham Device, Acuprime, Exeter, UK).
3. Treatment regimen	3a) Number of treatment sessions	5 sessions
	3b) Frequency and duration of treatment sessions	1 sessions per day for 5 days
4. Other components of treatment	4a) Details of other interventions administered to the acupuncture group	Conventional Western medicine management according to guideline: diuretics, nitroglycerin, angiotensin-converting enzyme inhibitors, angiotensin receptor blockers, beta blockers, aldosterone antagonists, ivabradine
	4b) Setting and context of treatment, including instructions to practitioners, and information and explanations to patients	The study will be conducted at the Kyung Hee University Medical Center. All patients will be admitted to the cardiac ward for treatment of acute heart failure. All information except patient allocated group will be provided to participants.
5. Practitioner background	5) Description of participating acupuncturists	Licensed KMDs with at least 2 years of clinical practice. The practitioners have studied acupuncture for more than 8 years and graduated from the University of Korean Medicine. Standardized operation procedures were written for practitioners to ensure identical treatments.
6. Control interventions	6a) Rationale for the control or comparator in the context of the research question, with sources that justify this choice	Based on consensus of the KMD, clinical experience, traditional acupuncture and meridian theory, and experimental/clinical articles
	6b) Precise description of the control or comparator. If sham acupuncture or any other type of acupuncture-like control is used, provide details as for Items 1 to 3 above.	For the control group, bilateral LI6, LI7, GB37, GB39, BL58 and BL59 will be stimulated 20 min per day for 5 days using PSD with a sham needle (0.25 mm × 40 mm sterilized stainless steel needle) that cannot penetrate the skin. It will be connected to an electrical stimulator without an electrical current.

*Abbreviations*: *KMD* Korean Medicine Doctor, *PSD* park sham device

#### Control group (PSD with a sham needle)

PSD is a validated sham acupuncture device composed of two tubes (Park tube, guide tube) that support the sham needle when penetrating the skin, and a sham needle indistinguishable from a real needle that cannot penetrate the skin [29, 36]. Double-sided tape will fasten the silicon base of the PSD. For the control group, bilateral LI6, LI7, GB37, GB39, BL58, and BL59 will be stimulated 20 min per day for consecutive 5 days using PSD with a sham needle connected to an electrical stimulator (ES-160, ITO, Japan) without electricity. LI6, LI7, GB37, and GB39 are known to be ineffective in cardiac disease [15, 16]. BL58 and BL59 do not decrease diuresis and edema and were selected through consensus of the KMDs. Other detailed information of the acupuncture treatment is described in the STRICTA checklist [35] (Table 2).

#### Co-interventions

The participants will be treated according to Western medicine acute HF management guidelines [2, 37]; diuretics, nitroglycerin, angiotensin-converting enzyme inhibitor, angiotensin receptor blockers, beta blockers, aldosterone antagonists, or ivabradine will be used according to the status of the participant. Other TEAM interventions that can affect results such as herbal medicine, moxibustion, transcutaneous electrical nerve stimulation, or pharmacopuncture will not be allowed.

### Outcome measurements: primary endpoint

A detailed outcome measurement schedule is presented in Table 1. The primary outcome of this trial is the cumulative diuretic dose administered from the date of admission to the date of discharge. The total doses of the treatment and control groups will be compared.

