**Methods:**

This protocol is for a randomized, sham controlled, patient- and assessor-blinded, parallel group, single center clinical trial that can overcome the limitations of previous trials examining acupuncture and heart failure. Forty-four acute decompensated heart failure patients admitted to the cardiology ward will be randomly assigned into the electroacupuncture treatment group (*n* = 22) or the sham electroacupuncture control group (*n* = 22). Participants will receive electroacupuncture treatment for 5 days of their hospital stay. The primary outcome of this study is the difference in total diuretic dose between the two groups during hospitalization. On the day of discharge, follow-up heart rate variability, routine blood tests, cardiac biomarkers, high-sensitivity C-reactive protein (hs-CRP) level, and N-terminal pro b-type natriuretic peptide (NT-pro BNP) level will be assessed. Four weeks after discharge, hs-CRP, NT-pro BNP, heart failure symptoms, quality of life, and a pattern identification questionnaire will be used for follow-up analysis. Six months after discharge, major cardiac adverse events and cardiac function measured by echocardiography will be assessed. Adverse events will be recorded during every visit.

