### Intervention

#### Study flow

If the participants voluntarily sign informed consent during admission to the cardiology ward, participants will be screened according to inclusion and exclusion criteria on the screening day. After the subject fulfills the criteria, the basic characteristics and prognostic factors of each participant will be evaluated. The subjects will be randomized into an intervention and a control group with a 1:1 allocation ratio on the same day; the screening day and Day 1 will usually be the same day. From Day 1 to Day 5, the participants will receive electroacupuncture treatment or sham electroacupuncture treatment once a day for consecutive 5 days according to their allocated group. After discharge, participants will visit KHMC three times. Visit (V1) will be 7 days after discharge. Visit 2 (V2) will be 28 days after discharge. Visit 3 (V3) will be 180 days after discharge. On the day discharge (Day 5) and V2, blood tests, quality of life (QOL), and a pattern identification questionnaire according to traditional East Asian medicine (TEAM) theory will be evaluated. On V3, cardiac function and MACE will be evaluated by echocardiography (Table 1). Participants will be withdrawn from the study if they 1) re-admit to hospital related to cardiac or kidney dysfunction 2) withdraw of consent by participants 3) worsening cardiac function 4) the principle investigator judged that participants can not continue the research.

**Table 1 Tab1:** Study schedule

Study period	Screening visit	Acupuncture treatment period					Follow-up period		
Visit	Screening	D1	D2	D3	D4	D5	V1	V2	V3
Informed consent	X								
Demographics and history collection	X								
Inclusion and exclusion criteria	X								
Randomization		X							
Physical examination and vital signs check	X	X	X	X	X	X	X	X	X
Body weight	X	X	X	X	X	X	X	X	X
Symptoms check (NYHA Functional Class)	X	X	X	X	X	X	X	X	X
Adverse events	X	X	X	X	X	X	X	X	X
Concomitant medication check	X	X	X	X	X	X	X	X	X
Routine blood test^a^	X		X			X		X	X
NT-pro BNP, hs-CRP	X					X		X	
Cardiac biomarkers^b^		X				X			
Cardiac function (echocardiography)	X								X
Electrocardiogram and HRV		X				X			
QOL and symptom questionnaire^c^		X						X	
Credibility and AES		X				X			
Blinding test		X				X			
Acupuncture treatment		X	X	X	X	X			

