*Abbreviations*: *AES* acupuncture expectancy scale, *D5* date of discharge, hs-*CRP* high-sensitivity C-reactive protein, *HRV* heart rate variability, *NT-pro BNP* N-terminal pro b-type natriuretic peptide, *NYHA* New York Heart Association, *QOL* quality of life, *V1* 7 days post-discharge ±5 days, *V2* 28 days post-discharge ±7 days, *V3* 180-days post discharge ±14 days

^a^Routine blood test: complete blood cell count and different counts (CBC, DC), blood urea nitrogen (BUN), creatinine, electrolyte (Na, K, Cl), total bilirubin, glucose, total protein, albumin, aspartate aminotransferase (AST), alanine aminotransferase (ALT)

^b^Cardiac biomarkers: atrial natriuretic peptide (ANP), ST2, catecholamine, vasoactive intestinal peptide (VIP), interleukin 6 (IL-6), vascular adhesion protein-1 (VAP-1)

^c^QOL and symptom questionnaire: EuroQol five dimensions questionnaire (EQ-5D), Minnesota Living with Heart Failure Questionnaire (MLHFQ), pattern identification questionnaire according traditional East Asian medicine theory

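### The primary diuretic total starts at admission rather than randomisation, so it includes doses treatment cannot affect, and its end is not reconciled with Day 5

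*Protocol article*

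**What the plan says.** All references are to the protocol article.

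- **Window.** *Outcome measurements: primary endpoint* defines the outcome as "the cumulative diuretic dose administered from the date of admission to the date of discharge".
- **Start of treatment.** *Recruitment period and method* recruits patients already admitted to the cardiology ward. *Study flow* says "If the participants voluntarily sign informed consent during admission to the cardiology ward, participants will be screened", then places randomisation and the first session on Day 1. It adds that "the screening day and Day 1 will usually be the same day". That links screening to Day 1; nothing links either to the admission date.
- **End of treatment.** *Study flow* writes "On the day discharge (Day 5) and V2", and the key to Table 1 likewise identifies D5 with discharge. The abstract says "Participants will receive electroacupuncture treatment for 5 days of their hospital stay".
- **Analysis.** *Statistical analysis* compares totals by t-test or Mann-Whitney test, uses ANCOVA only if a baseline characteristic differs significantly between groups, and fills missing values by last observation carried forward (LOCF).
- **Withdrawal.** *Study flow* lists worsening cardiac function among the withdrawal reasons.
- **Direction.** *Discussion* treats lower diuretic use as evidence of benefit.

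**The concern.** A total that opens before randomisation contains a component on which the two arms cannot differ except by chance. Its variation between patients goes straight into the error term of the only primary comparison. The plan does not remove it routinely, because adjustment depends on a baseline significance test, and such a test has little power to detect imbalance at 22 per group.

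The closing date matters too. A cumulative dose grows with days counted, and the article does not say which window applies when discharge is not on Day 5. Finally, because a low total is read as favourable, a total that stops early for a bad reason would point the wrong way if it were taken as complete.

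**Working it through.** **1. Reproduce the planned sample size.** Inputs from *Sample size calculation*: 223 (SD 26) mg and 256 (SD 39) mg, two-sided α = 0.05, power 80%, about 20% dropout.

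- Pooled SD = √((26² + 39²)/2) = √((676 + 1521)/2) = √1098.5 = 33.14 mg.
- Difference = 256 − 223 = 33 mg; d = 33/33.14 = 0.996.
- Noncentral t: 17 per group gives 80.4% power and 16 gives 77.8%, so n = 17.
- 17/0.8 = 21.25, rounded up to 22 per group, 44 in total.

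The stated 17, 22 and 44 all reproduce. The arithmetic is not in question.

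**2. What pre-randomisation dosing does to the comparison.** If every patient received the same extra dose c before Day 1, the difference would be (256 + c) − (223 + c) = 33 mg, unchanged. Only the spread of c between patients matters. If that spread has SD e, is independent of arm and is not already in the planning SD, the total SD becomes √(1098.5 + e²). The article gives no value for e, so the range is an assumption:

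| Added SD e (mg) | Total SD (mg) | Power at 17 per group | n per group for 80% |
|---|---|---|---|
| 0 | 33.1 | 80% | 17 |
| 10 | 34.6 | 77% | 19 |
| 20 | 38.7 | 67% | 23 |
| 30 | 44.7 | 55% | 30 |
| 40 | 51.9 | 44% | 40 |

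The same cost can be seen as chance imbalance. With 22 per group, the standard error of the between-arm difference in mean pre-randomisation dose is e × √(2/22) = 0.30e. That is 3.0 mg at e = 10 and 12.1 mg at e = 40, against a planned effect of 33 mg.

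**3. The end of the window.** If all patients leave on Day 5, the post-randomisation part is five days for everyone and only the lead-in varies. If not, the endpoint and the schedule describe different windows. For scale only, assume the planning means accrue evenly over 5 days: (223 + 256)/2 = 239.5 mg, and 239.5/5 = 47.9 mg/day. A between-arm difference in mean stay of 33/47.9 = 0.69 day would then equal the planned effect. Over an assumed 7-day stay the figures are 239.5/7 = 34.2 mg/day and 33/34.2 = 0.96 day.

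**4. A partial total carried forward.** Assume a 256 mg total accrues evenly over 5 days, stops at day 2 and is carried forward as final. Each such patient lowers a 22-patient arm mean by 256 × (1 − 2/5)/22 = 7.0 mg, or 21% of 33 mg. Stopping at day 1 gives 9.3 mg and at day 3 gives 4.7 mg. A simulation with no true effect (22 per arm, SD 33.14 mg, truncation at day 2 in one arm only) gave these chances of a significant result favouring the truncated arm:

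| Patients truncated | t-test | Mann-Whitney |
|---|---|---|
| 0 | 2.5% | 2.6% |
| 1 | 4.6% | 3.9% |
| 2 | 9.1% | 6.0% |
| 3 | 18.5% | 9.2% |
| 4 | 33% | 14.5% |

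This is the one-sided worst case. Equal truncation in both arms would mainly add noise.

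**The case against.** The whole-stay total is a reasoned choice. *Background* says that hospitalisation diuretic dose has been recorded in earlier acute heart failure trials, and a review recommended reporting it. Length of stay after randomisation is itself an outcome, so an effect that acts through a shorter stay can belong in the estimand. This stands: running to discharge is defensible, and a fixed five-day window is a trade-off rather than a correction. It does not justify starting before randomisation.

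The planning SDs are also hospitalisation totals and may already carry early dosing and variation in stay. This stands as well. The power losses above are upper readings for each assumed spread, and it is not shown that the sample size ignores this variance.

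A reader might infer more than the article supports:

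- *That a pre-randomisation day adds 34 to 48 mg of noise, as large as the effect.* That is a mean. A shift common to both arms cancels.
- *That the endpoint mainly measures days in hospital.* No distribution of stay is given, the schedule labels Day 5 as discharge, and the attending physician is blinded, which limits differential discharge decisions.
- *That early death or withdrawal counts as success.* The outcome is continuous, and no rule says this. Withdrawal truncates the total only if ward dosing stops being collected, which is not stated. Readmission, another withdrawal reason, comes after discharge. No in-hospital death rate is given, and detailed handling of death may sit in documents not shown.
- *That milligrams are added across different diuretics.* The article does not say so. A conversion rule is something an article commonly leaves out.

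**Conclusion.** The point holds in a limited form. The article itself fixes a window that opens at admission, so this is not a detail left to a fuller document, and doses given before Day 1 lie inside the primary endpoint. The consequence is lower precision and exposure to chance imbalance, not bias. Power at 17 per group would fall from 80% to between 77% and 44% for an added SD of 10 to 40 mg. That range is assumed, and the loss is smaller to the extent that the planning SDs already include this variation.

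Day 5 and discharge need reconciling with the endpoint definition. The LOCF problem is conditional: it biases the comparison only if LOCF is applied to a running total, ward dosing is no longer collected after withdrawal, and truncation differs by arm. The planned sample size is correctly computed from its inputs.

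**What to change.** 1. Start the primary count at randomisation.
2. Include the pre-randomisation diuretic dose as a prespecified covariate in the primary analysis, whatever the baseline tests show. This makes an adjusted model primary in place of the unadjusted t-test or Mann-Whitney test.
3. Reconcile *Study flow*, the key to Table 1 and *Outcome measurements: primary endpoint*, stating which window applies when discharge is not on Day 5.
4. Continue collecting in-hospital dosing after withdrawal where consent allows, and do not carry a partial cumulative total forward as the final value.
5. As a sensitivity analysis, report the total from randomisation to the end of Day 5, alongside body-weight change, which Table 1 already schedules daily.

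The cost is modest. Daily doses should be available from the ward chart, and Table 1 already schedules a daily medication check. It is nevertheless an amendment to the primary endpoint while recruitment is open, so it must be made and dated before unblinding. The planning figures would then refer to a slightly longer window than the endpoint, which should be acknowledged beside the sample size.

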### Recruitment period and method

We will recruit participants who are admitted to the cardiology ward of Kyung Hee Medical Center (KHMC) for treatment of acute HF. Attending physicians (Western medicine cardiologists) will check the inclusion criteria and inform patients or guardians about the acupuncture clinical trial. If the patient or guardian agrees to participate in the trial, written informed consent will be obtained by attending physicians. Recruitment is expected to continue from March 2016 until May 2019. We will not use other advertising methods such as a homepage, bulletin boards, or mass media.

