### Type of participants: inclusion and exclusion criteria

#### Inclusion criteria

Participants who satisfy the following criteria will be recruited:Over 40 years of age, with written informed consent.Acute HF patient presenting with dyspnea related to cardiogenic pulmonary edema and in need of diuretic treatment.Systolic blood pressure > 95 mmHg at admission.B-type natriuretic peptide (BNP) > 150 pg/mL or NT-pro BNP > 600 pg/mL.

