### Statistical analysis

The primary outcome of our study is the cumulative amount of diuretic administered to each group. After a normality test, the total amount will be compared by an independent *t*-test (parametric) or a Mann-Whitney U test (non-parametric) according to the normality of the data. If the baseline characteristic is significantly different between the two groups, an analysis of covariance (ANCOVA) will be used to adjust the baseline difference. In baseline characteristics and secondary outcome analysis, binary outcomes will be compared by a chi-square test or Fisher’s exact test. Continuous outcomes will be compared by an independent *t*-test (parametric) or Mann-Whitney U test (non-parametric). MACE will be also be analyzed using the survival analysis method. Statistical analysis will be performed using the R package by a blinded statistician. A 5% significance level will be used. Missing values will be replaced by the last observation carried forward method. If there are more than 20% of drop out participants, sensitivity analysis will be conducted including the data.

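### The primary outcome counts diuretic given between admission and randomisation, and the analysis does not commit to adjusting for it: avoidable noise of unknown size, not bias

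*Protocol article*

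**What the plan says.** The section on the primary endpoint defines the outcome as "the cumulative diuretic dose administered from the date of admission to the date of discharge". The statistical analysis section repeats it without a start point: "The primary outcome of our study is the cumulative amount of diuretic administered to each group".

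Entry to the trial comes after the start of that window. The recruitment section says "We will recruit participants who are admitted to the cardiology ward of Kyung Hee Medical Center (KHMC) for treatment of acute HF". The study flow section continues: "If the participants voluntarily sign informed consent during admission to the cardiology ward, participants will be screened according to inclusion and exclusion criteria". Baseline evaluation follows, and then "The subjects will be randomized into an intervention and a control group with a 1:1 allocation ratio on the same day". The first session is on Day 1. On timing, the same section says that "the screening day and Day 1 will usually be the same day". Every participant must be "in need of diuretic treatment" under the inclusion criteria.

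The statistical analysis section compares totals by t-test or Mann-Whitney test, depending on a normality test. It turns to ANCOVA only if a baseline characteristic differs significantly between groups. Diuretic dose before randomisation is not named as a baseline characteristic or as a covariate.

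**The concern.** The outcome window opens before allocation. Whatever diuretic a patient receives between admission and randomisation was given before electroacupuncture or sham could act on it, so it says nothing about the treatment. It still counts in full in the primary total.

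Precision is what is at stake. Patients who wait longer for randomisation, or who are treated more heavily on arrival, carry a larger fixed component into their total. With 22 per arm that component need not balance by chance. Left unadjusted, it widens the confidence interval and can move the estimate in either direction. The analysis has a route to adjustment, but only through a significance test of baseline differences, which is a poor trigger at this sample size.

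**Working it through.** **1. The plan's own figure.** The inputs come from the sample size section: means 256 and 223 mg, SDs 39 and 26 mg, two-sided 5%, 80% power, dropout 20%.
- Difference = 256 − 223 = 33 mg.
- Pooled SD = √((39² + 26²)/2) = √1098.5 = 33.1 mg. Standardised difference = 33/33.1 = 0.996.
- The noncentral t calculation gives 17 per arm (power 80.4%), and 17/0.8 rounds up to 22. The stated 17 and 22 reproduce.

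Both planning means are described as cumulative furosemide during hospitalisation. The sample size therefore matches the stated outcome in form, and the arithmetic is not in question.

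**2. Effect on the expected difference.** Write total dose Y = P + L, with P given before randomisation and L after. Randomisation makes the mean of P the same in both arms, so the expected difference in Y equals the expected difference in L. Including P leaves the expected mg difference unchanged.

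**3. Effect on variance.** Var(Y) = Var(P) + Var(L) + 2Cov(P, L). An unadjusted test carries all of this. If ρ is the within-arm correlation between P and Y, adjusting for P multiplies the standard error by about √(1 − ρ²), before the loss of one degree of freedom.

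The article gives nothing from which to estimate ρ. As an illustration only, take 33.1 mg as the SD of the whole-stay total and assume that P is uncorrelated with L:

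| Assumed SD of P (mg) | Residual SD after adjustment (mg) | SE of difference, 17 per arm (mg) |
|---|---|---|
| 0 | 33.1 | 33.1 × √(2/17) = 11.4 |
| 10 | √(1098.5 − 100) = 31.6 | 10.8 |
| 20 | √(1098.5 − 400) = 26.4 | 9.1 |

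Under these assumptions the SD of P cannot exceed 33.1 mg. The range runs from no gain to a useful one, and the documents do not say where the trial lies.

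**4. What the conditional ANCOVA would miss.** A baseline difference in P reaches 5% significance only if it exceeds t × √(2/n) standard deviations.
- 22 per arm: 2.02 × √(2/22) = 0.61 SD.
- 17 per arm: 2.04 × √(2/17) = 0.70 SD.

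Even if P were among the characteristics tested, imbalances up to about 0.6 to 0.7 SD would go unadjusted.

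**5. Equivalence of the two remedies.** Fit Y = a + b·group + c·P + e. Subtracting P from both sides gives L = a + b·group + (c − 1)·P + e. The residuals are the same, so b, its standard error and its p-value are identical. With P as a linear covariate, the whole-stay and post-randomisation outcomes give the same treatment result. This does not carry over to the unadjusted t-test or the Mann-Whitney test, where the choice of window changes the answer.

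**The case against.** The strongest reply is that the point may be of little consequence. Screening, randomisation and Day 1 usually coincide, the blood pressure criterion is read at admission, and the inclusion criteria require a need for diuretics, not that diuretics have already been given. A short gap and a small pre-randomisation dose are plausible. This stands as a limit on size. It does not remove the point, because the same-day sentence links screening to Day 1 and not admission to Day 1. A window that opens on the admission date also includes any doses given that day before allocation.

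It is also fair to say that chance imbalance is not bias. It is part of the variance that the t-test already allows for, and type I error stays at 5%. That stands too. The case for adjustment rests on precision.

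A reader might infer three stronger things that the documents do not support:
- **That the group difference is diluted.** The expected mg difference is unchanged (step 2). Only the relative difference and the precision can suffer.
- **That the trial has a calculable loss of power.** This would mean scaling the 33 mg down by an assumed untreated share. The planning figures are already whole-stay doses, so the scaling presumes more untreated early dose here than in the source trial, and nothing in the article says that.
- **That early doses fall outside data collection.** Table 1 starts the medication check at screening, but a check at screening, together with history taking, can look back over the admission.

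**Conclusion.** The point holds as one of precision and clarity. The primary outcome includes dose that the intervention cannot affect, and the analysis does not commit to adjusting for it. The comparison remains unbiased and the sample size calculation reproduces. The cost is extra between-patient variance and exposure to chance imbalance in 44 patients. Its size cannot be stated without the admission-to-randomisation interval and the dose given in it, and it may be close to nil if randomisation follows admission quickly. The conclusion rests on the article's wording of the outcome window and the order of events, and on pre-randomisation dose not being named as a covariate. The change is worth making because it is cheap, not because the result would otherwise be invalid.

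**What to change.** In the statistical analysis section, pre-specify that the primary comparison of cumulative diuretic dose uses ANCOVA with diuretic dose from admission to randomisation as a covariate, whatever the result of any baseline test. Take the date and time of each dose from the ward drug chart, including for participants already enrolled, and split the total at the time of randomisation.

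Redefining the outcome as dose from randomisation to discharge, with the whole-stay total kept as a secondary outcome, is optional. Under the linear adjustment it gives the same estimate, standard error and p-value. It makes the outcome easier to interpret, at the price of changing a registered outcome. If an unadjusted or rank-based analysis is kept alongside, state which window it uses.

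Make the change by a blinded amendment. The article describes the trial as still recruiting and the statistician as blinded, so this is feasible. The cost is one covariate (one degree of freedom) and a look-back at drug charts. It needs no extra patients or visits and no change in treatment.
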